# Angiographic and clinical comparison of novel Orsiro Hybrid sirolimus-eluting stents and Resolute Integrity zotarolimus-eluting stents in all-comers with coronary artery disease (ORIENT trial): study protocol for a randomized controlled trial

**DOI:** 10.1186/1745-6215-14-398

**Published:** 2013-11-20

**Keywords:** Drug-eluting stent, Orsiro hybrid stent, Zotarolimus-eluting stent, Coronary heart disease

## Abstract

**Background:**

The Orsiro Hybrid sirolimus-eluting stent is a newly developed third-generation drug-eluting stent, featuring a unique dual-polymer mix. An active bioabsorbable polymer delivers the anti-proliferative drug, sirolimus, via controlled release, while a passive biocompatible polymeric coating shields the metallic strut from surrounding tissue, preventing interaction. To date, the Orsiro Hybrid sirolimus-eluting stent has excelled in terms of late lumen loss at 9 months in a first-in-man single-arm trial. However, the efficacy and safety data for Orsiro Hybrid sirolimus-eluting stents in a broader population of all-comers are limited. The present study offers an angiographic and clinical comparison of the Orsiro Hybrid sirolimus-eluting stent and the Resolute Integrity zotarolimus-eluting stent in the treatment of patients with coronary artery disease.

**Methods/design:**

The ORIENT trial is a multicenter, randomized, open-label, parallel-arm study designed to demonstrate the non-inferiority of the Orsiro Hybrid sirolimus-eluting stent relative to the Resolute Integrity zotarolimus-eluting stent. A total of 375 patients with a spectrum of coronary artery disease will undergo prospective, random assignment to a Orsiro Hybrid sirolimus-eluting stent or Resolute Integrity zotarolimus-eluting stent (2:1 ratio), for a primary endpoint of in-stent late lumen loss at 9 months by quantitative coronary angiography. Secondary 12-month clinical endpoints are death, target lesion revascularization, target vessel revascularization, myocardial infarction, stent thrombosis and target lesion failure (a composite of cardiac death, target lesion revascularization and target vessel-related myocardial infarction).

**Discussion:**

The ORIENT trial is the first study to date comparing the Orsiro Hybrid sirolimus-eluting stent with the Resolute Integrity zotarolimus-eluting stent for efficacy and safety in a population of all-comers with coronary artery disease.

**Trial registration:**

Clinicaltrials.gov NCT01826552

## Background

Since the introduction of the first-generation drug-eluting stent (DES), rates of restenosis after percutaneous coronary intervention (PCI) have declined dramatically [1-3]. However, there are concerns that the benefit of a DES in reducing restenosis is at the expense of thrombogenic risk. Hence, efforts to reduce both restenosis and thrombosis are ongoing and have resulted in a flurry of second-generation devices made with biocompatible but non-absorbable polymers, as well as third-generation models incorporating bioabsorbable polymers [4,5].

The recently launched Orsiro Hybrid sirolimus-eluting stent (Orsiro SES, Biotronik AG, Bulach, Switzerland) features a unique hybrid polymer laminate over thin cobalt chromium struts. The active BIOlute® bioabsorbable polymer matrix is embedded with the anti-proliferative drug sirolimus and releases the drug in a controlled manner after implantation. This component degrades over time, leaving behind only the PROBIO® encapsulated stent. The passive PROBIO® coating confers a protective interface that guards against a reaction between the stent’s metal framework and the surrounding tissues [6]. Although the Orsiro SES has excelled in terms of late lumen loss at 9 months in a first-in-man single-arm trial (BIOFLOW-I trial) [7], randomized controlled trials evaluating its efficacy and safety are limited to date.

The ORIENT Trial will be an angiographic and clinical comparison of the Orsiro SES, an innovative third-generation DES, with the Resolute Integrity zotarolimus-eluting stent (ZES-I, Medtronic Cardiovascular, Santa Rosa, CA, USA), the latest second-generation DES, in the treatment of patients with coronary artery disease (CAD).

## Methods/design

### Study design

This is a prospective, randomized, open-label, and parallel-group multicenter trial designed to test the non-inferiority of the Orsiro SES relative to the ZES-I in preventing late lumen loss 9 months after the index procedure (Figure 1). A total of 375 patients exhibiting a wide spectrum of CAD will be enrolled at eight centers in Korea. Participants will be monitored clinically at months 1, 6, 9 and 12. Investigators may conduct this follow-up as telephone interviews or office visits. An angiographic follow-up to determine late lumen loss is advised at 9 months post-procedure or earlier should the patient experience ischemic symptoms or show non-invasive evidence of ischemia.

**Figure 1 F1:**
[figure not shown]
**ORIENT trial algorithm.** ACC, American College of Cardiology; AHA, American Heart Association; CAG, coronary angiography; DES, drug-eluting stent; ESC, European Society of Cardiology; EACTS, European Association for Cardio-Thoracic Surgery; F/U, follow-up; QCA, quantitative coronary angiography; SCAI, The Society for Cardiovascular Angiography and Interventions; SES, sirolimus-eluting stent; ZES, zotarolimus-eluting stent.

This trial is investigator-initiated, with grant support from the Biotronik Korea Co, Korea. Other than financial sponsorship, the company has no role in protocol development or the implementation, management, data collection and analysis of this study. The authors alone are responsible for the design and execution of the trial, related statistical analyses and all aspects of manuscript preparation, including drafting, editing and final content. This study will be conducted according to the principles outlined in the Declaration of Helsinki. All patients must provide written informed consent. This study protocol has been approved by the institutional review board of Seoul National University Bundang Hospital and registered at http://www.clinicaltrials.gov (NCT01826552).

### Study population and entry criteria

Prospective subjects are those at least 18 years of age, presenting with symptomatic CAD (including acute coronary syndrome) and coronary lesions >50%, in whom PCI with DES implantation is indicated, based on the current recommendations of ACC/AHA/SCAI and ESC/EACTS guidelines or the clinical judgment of the interventional cardiologist (Table 1) [8,9]. Whether the PCI is indicated based on current recommendations or not will be separately recorded. Inclusion and exclusion criteria will be graded to minimize exclusion of patients, thus reflecting the population at large. All participants will be randomly assigned in a 2:1 ratio to either the Orsiro SES or ZES-I group. To generate comparable groups relative to known and unknown risk factors, randomization will be independently conducted online via a web-based application (T&W Software, Seoul, Korea). The randomization will be balanced and stratified by participating center and allocated treatment groups.

**Table 1 T1:** Eligibility criteria for the ORIENT trial

**Inclusion criteria**	● Patient age ≥18 years
	● Ability to acknowledge verbally the risks, benefits and treatment ramifications in receiving the Orsiro Hybrid® or Resolute Integrity® stent
	● Written informed consent given by legally authorized agent prior to any study-related procedure
	● Indication for use of drug-eluting stent based on ACC/AHA/SCAI and ESC/EACTS guidelines and/or clinical judgment of interventional cardiologist.
	● Target lesion(s) in coronary artery or graft vessel with estimated reference diameter ≥2.5 mm and ≤5.0 mm
	● Target lesion(s) amenable to percutaneous coronary intervention
**Exclusion criteria**	● Known hypersensitivity or contraindication to any of the following agents: heparin, aspirin, clopidogrel, sirolimus, zotarolimus, cobalt chromium or contrast media^a^
	● Inability to tolerate aspirin or clopidogrel for 1-year duration of study
	● Systemic (intravenous) use of sirolimus or zotarolimus within 12 months
	● Females with childbearing potential (unless negative by a recent pregnancy test) or anticipating pregnancy following study enrollment
	● History of bleeding diathesis, known coagulopathy (including heparin-induced thrombocytopenia), or refusal of blood transfusions
	● Gastrointestinal or genitourinary bleeding within prior 3 months, or major surgery within 2 months
	● Planned major non-cardiac surgery within designated study period
	● Cardiogenic shock (Killip class IV)
	● Symptomatic heart failure, precluding coronary angiography in a supine position
	● Non-cardiac co-morbid conditions limiting life expectancy (to <1 year) or potentially undermining protocol compliance (as judged by the site investigator)
	● Active participation in another drug- or device-related investigational study where the primary endpoint follow-up is ongoing
	● Unwillingness or inability to comply with protocol procedures

^a^Patients with documented sensitivity (such as a rash) to contrast media that is amenable to premedication with steroids and diphenhydramine may still be enrolled. However, true anaphylaxis on prior exposure to contrast media is grounds for exclusion.

### Outcome measurements and definitions

The primary endpoint of the trial is in-stent late lumen loss at 9 months, as measured by quantitative coronary angiography (QCA). Secondary angiographic endpoints at 9 months are in-segment late lumen loss, percentage diameter stenosis (%DS) and binary restenosis. Secondary clinical endpoints include all-cause and cardiac deaths, clinically driven target lesion revascularization (TLR), target vessel revascularization (TVR), myocardial infarction (MI) (target or non-target vessel-related), stent thrombosis and target lesion failure (TLF, a composite of cardiac death, TLR and target vessel-related MI) at 12 months [10,11]. Revascularization is considered clinically driven if the follow-up angiographic diameter stenosis ≥50%, and there is at least one of the following: (1) history of recurrent angina pectoris, presumably related to the target vessel, (2) objective signs of ischemia at rest or during exercise testing (or equivalent), presumably due to the target vessel, (3) abnormal invasive functional diagnostic testing or (4) TLR or TVR with ≥70% diameter stenosis, even without any of the aforementioned ischemic signs/symptoms [10,12].

To reduce the chance of the so-called oculostenotic reflex, whereby rates of repeated revascularization are disproportionately high, investigators will be encouraged to perform a non-invasive stress test or invasive functional diagnostic test (for example, fractional flow reserve) prior to a decision regarding repeated revascularization and they will adhere strictly to a clinically driven revascularization protocol. In addition, the specified indication of revascularization and the number of TVRs or TLRs that are performed without a non-invasive stress test will be separately recorded.

### Coronary angiography and percutaneous coronary intervention

Coronary interventions will be performed according to current standard techniques. Aside from random stent assignment, any pre-dilatation, post-stenting adjunctive balloon inflation, and intravascular ultrasound or glycoprotein IIb/IIIa inhibitor use will be at the operators' discretion. All patients will receive aspirin (300 mg) and a loading dose of clopidogrel (300 mg to 600 mg) prior to the procedure, unless these are routinely taken, for at least 1 week beforehand. Heparin sufficient to sustain activated clotting time at >250 sec will be administered intravenously in boluses during the procedure. All patients will be given aspirin indefinitely (at least 100 mg/day) and clopidogrel (75 mg/day) for a minimum of 12 months after the index procedure.

### Quantitative coronary angiography

The coronary angiography at baseline, immediately after the procedure and at follow-up will be analyzed using an automated edge-detection system (Cardiovascular Angiography Analysis System 5.7.1; Pie Medical Imaging Systems, Maastricht, the Netherlands) at the core laboratory in Seoul National University Bundang Hospital by an experienced technician who is blinded to the study. The minimal lumen diameter (MLD), reference vessel diameter, %DS, acute gain (difference in MLD pre- and post-implantation of the stent), late lumen loss (difference in post-procedural and follow-up MLD) and binary restenosis (≥50% stenosis at the follow-up angiography) will be measured [13]. All QCA assessments of target lesions will be in-stent and in-segment (stent plus 5-mm proximal and distal margins).

### Statistical considerations

#### Sample size calculation

To test the primary hypothesis (non-inferiority of the Orsiro SES relative to the ZES-I by 9-month in-stent late lumen loss), we assumed a mean late loss of 0.3 mm (SD 0.54 mm) for both stents, which was extrapolated from the QCA results for the Endeavor Resolute® (ZES-R) from the RESOLUTE US trial [14]. The ZES-I and ZES-R devices use same the delivery drug (zotarolimus) and basic design, namely a biocompatible polymer (BioLinx®) mounted on a cobalt chromium platform. For non-inferiority testing, with a 0.2 mm non-inferiority margin, type I error at 0.05 (one-sided), 90% statistical power, 2:1 sampling ratio (Orsiro SES:ZES-I) and an expected 30% dropout rate (at the 9-month follow-up angiography), a total of 375 patients (Orsiro SES, 250; ZES-I, 125) were deemed necessary to execute this study. To avoid interlesion clustering of restenosis in patients receiving stents for multiple lesions, which would have required correction with multilevel generalized estimating equations, only one randomly selected lesion will be used in the analysis of in-stent late lumen loss [15,16]. Sequential superiority testing will be performed if non-inferiority for in-stent late lumen loss is met. This number of patients would also have 92% power to detect superiority with an in-stent late lumen loss difference of 0.2 mm between the groups at a two-sided alpha level of 0.05.

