#### Statistical analysis

All primary and secondary endpoints will first be analyzed on an intention-to-treat basis (all patients according to the assigned treatment groups), and secondarily, per protocol/treatment. The per protocol analysis is aimed at patients completing the study protocol as initially assigned, without significant breach or crossover, whereas the per treatment analysis addresses the treatment modality received, regardless of initial device assignment. Per protocol/treatment analyses are intended solely for descriptive comparisons, not as tests of the working hypothesis. For the intention-to-treat analysis, all patients giving written informed consent and randomly assigned for the study will be used in the analysis sample, whether or not the treatment rendered was correct or crossover occurred. The endpoints will also be subjected to per patient and per lesion analyses as feasible.

The null hypothesis will be evaluated on a non-inferiority basis, using an independent sample t-test of the mean late lumen loss in both groups. Non-inferiority is defined by a one-sided alpha of 5% and a difference in late lumen loss ≤0.2 mm. TLF, TLR, TVR, MI and stent thrombosis rates at 12 months will be analyzed with a χ2-test, generating Kaplan–Meier survival estimates for time to events of TLF, TLR, TVR and MI at 12 months. Acute success (device, lesion and procedure) analysis will utilize a χ2-test as specified. An independent t-test or χ2-test will be invoked as needed to assess in-stent/in-segment %DS and in-stent/in-segment binary restenosis at 9 months. In addition, exploratory subgroup analysis will be performed, rather than pre-specified subgroup analysis.

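### The stated design inputs call for about 403 to 408 randomised patients, not 375; at 375 with 30% dropout the non-inferiority power is about 88%, not 90% (minor)

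*Protocol article*

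**What the plan says.** The section Sample size calculation gives every input that the calculation needs:

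- Means and SD: "we assumed a mean late loss of 0.3 mm (SD 0.54 mm) for both stents", so the assumed true difference is zero.
- Design: "0.2 mm non-inferiority margin, type I error at 0.05 (one-sided), 90% statistical power, 2:1 sampling ratio".
- Attrition and result: "an expected 30% dropout rate (at the 9-month follow-up angiography), a total of 375 patients (Orsiro SES, 250; ZES-I, 125) were deemed necessary".

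The section Statistical analysis repeats the error rate and margin: "Non-inferiority is defined by a one-sided alpha of 5% and a difference in late lumen loss ≤0.2 mm". It names the test as one carried out "using an independent sample t-test of the mean late lumen loss in both groups".

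One randomly chosen lesion per patient enters the primary analysis, so the calculation contains no clustering term. The total of 375 also appears under Study design and in the abstract: "A total of 375 patients with a spectrum of coronary artery disease will undergo prospective, random assignment".

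The sample size paragraph closes by giving the same number of patients 92% power for superiority, for a 0.2 mm difference at two-sided alpha 0.05.

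**The concern.** A reader can recompute the sample size from the paragraph alone, and the result is not 375. Sample size, dropout and power are linked: once two are fixed, the third follows. Here all three are stated and they do not agree.

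The paragraph is the only justification given for the enrolment target. As written, it tells the reader that 90% power on the primary endpoint survives a 30% loss of follow-up angiograms. What is at stake is the accuracy of that statement. The validity of the test is not in question.

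**Working it through.** **Inputs** (Sample size calculation; alpha, margin and test confirmed under Statistical analysis): SD 0.54 mm, true difference 0, margin 0.2 mm, one-sided alpha 0.05 (z = 1.645), power 90% (z = 1.282), allocation 2:1, dropout 30%.

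**1. Evaluable patients needed, normal approximation**

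n(control) = (1 + 1/2) × [0.54 × (1.645 + 1.282) / 0.2]² = 93.6, rounded up to 94.

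The test arm needs 2 × 94 = 188, for a total of 282 (280.9 before rounding).

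**2. Evaluable patients needed, t-test**

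With the noncentral t distribution, the smallest exact 2:1 design that reaches 90% is 190:95, a total of 285.

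**3. Allowing for 30% dropout**

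- Normal: 282 / 0.70 = 402.9, so 403.
- t-test: 285 / 0.70 = 407.1, so 408 (a multiple of three, which keeps 2:1).

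The stated 375 is 28 below 403, which is 7%.

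**4. Attempts to reach 375**

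| Route | Total |
|---|---|
| Stated inputs, n / (1 − 0.30) | 403 (normal), 407 to 408 (t) |
| 25% dropout, unrounded n: 280.9 / 0.75 | 374.6, so 375 |
| Multiplying by 1.30 instead of dividing by 0.70 | 367 (282 × 1.3), 371 (285 × 1.3) |
| One-sided alpha 0.025, 80% power, 30% dropout | 369 |
| 1:1 allocation, 30% dropout | 357 |

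The multiplication route, worked by arm from 190:95, gives 247 and 123.5, which could have been rounded up to 250 and 125. Every route that comes near 375 either changes a stated input or inflates incorrectly.

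**5. Non-inferiority power that 375 delivers**

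With 30% lost, 375 × 0.70 = 262.5, so about 262 evaluable (175:87).

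SE = 0.54 × √(1/175 + 1/87) = 0.0708

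Power = Φ(0.2 / 0.0708 − 1.645) = 0.881; by noncentral t, 0.879.

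Taking the control arm as 87.5 gives 0.882 and 0.880.

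**6. Dropout that 375 can carry at 90% power**

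- t-test: 1 − 285/375 = 24.0%.
- Normal: 1 − 282/375 = 24.8%.

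**7. Superiority power in the same paragraph** (0.2 mm difference, two-sided 0.05)

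| Evaluable | Normal | t-test |
|---|---|---|
| 250:125 (no dropout) | 92.2% | 92.1% |
| 175:87 (30% dropout) | 80.6% | 80.3% |

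The 92% is therefore reproduced, but only with no dropout at all. Under the same no-dropout condition the non-inferiority power would be about 96%. The paragraph thus allows for dropout in one calculation and not in the other.

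**The case against.** The strongest reply is that the discrepancy hardly matters. The loss is about 2 points of power. At 375 randomised with 30% dropout, an SD of about 0.52 mm instead of 0.54 mm would restore 90%, and the article says that its SD was extrapolated from trial results for a related earlier stent. A difference of 0.02 mm is small for an assumption of that kind. This stands, and it is why the point is minor. It does not make the sentence correct, because power is stated for the inputs given.

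Three stronger readings are tempting, and the article supports none of them.

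- A reader might infer that the trial is seriously underpowered and must enrol more patients. Power of about 88% does not support that.
- A reader might infer that the true planning figure was 25% dropout, because it reproduces 375. That percentage appears nowhere in the article, and the multiplication slip with rounding is also plausible. The source of the error cannot be identified.
- A reader might infer that the investigators thought they had a 30% reserve, or that a formal follow-up target is now needed. The article gives 30% as the loss it expects and claims no reserve beyond it. A follow-up target would be an optional operational choice; the inconsistency does not require one.

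**Conclusion.** The point holds as a minor error in a stated figure. On the article's own inputs, 90% power with 30% angiographic dropout needs about 403 randomised patients (normal) or 407 to 408 (t-test). With 375, non-inferiority power is about 88%. The sample size shortfall of about 7% is clear under either method; the consequence for power is about 2 points.

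The superiority figure in the same paragraph shows the larger gap, 92% against about 80 to 81%, because the expected dropout was left out of it. Read as applying to 375 evaluable patients, the 92% is correct, but it does not describe the trial as planned.

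The conclusion assumes equal true means for non-inferiority, a common SD of 0.54 mm, dropout equal in the two arms, and an analysis of patients with a follow-up angiogram. The margin, the test and the type I error are untouched.

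**What to change.** Keep enrolment at 375 and restate the power. For example:

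> With 375 patients randomised 2:1 and 30% without 9-month angiography, about 262 are evaluable (175:87) and non-inferiority power is about 88%. Power of 90% by t-test needs about 285 evaluable patients, that is, dropout of no more than about 24%.

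In the same paragraph, give the superiority power as about 80 to 81% after 30% dropout. If the 92% is kept, say that it assumes all 375 patients are evaluable.

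If the authors can establish that the dropout rate was the misprinted item, they should correct that figure instead and align both power statements with it.

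The cost is two edited sentences and slightly less favourable stated power. No extra patients are needed, and the margin, alpha and analysis do not change.

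### Per-lesion analyses are planned, but the only tests named for the lesion-level secondary endpoints assume independence, although the protocol says such data need a clustering correction

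*Protocol article*

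**What the plan says.** Under Sample size calculation, the protocol article recognises that lesions in one patient are correlated with respect to restenosis. It says that analysing several lesions per patient is something "which would have required correction with multilevel generalized estimating equations". It sidesteps this by stating that "only one randomly selected lesion will be used in the analysis of in-stent late lumen loss". As worded, the rule applies to in-stent late lumen loss only.

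Under Statistical analysis, it adds: "The endpoints will also be subjected to per patient and per lesion analyses as feasible". That sentence names no method. The next paragraph names tests by endpoint:

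- Late lumen loss: independent-sample t-test.
- In-stent and in-segment percentage diameter stenosis and binary restenosis: "An independent t-test or χ2-test will be invoked as needed".
- Acute success, listed for device, lesion and procedure: χ2-test.

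No clustering correction is named for any endpoint in that section. In-segment late loss is a secondary endpoint, and the one-lesion rule does not mention it.

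**The concern.** The two sections do not fit together. One says that multi-lesion data need a correction. The other plans lesion-level results and names only tests that treat every observation as independent. Restenosis, the outcome for which the first section raises clustering, is among the endpoints given an uncorrected test without the one-lesion rule.

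Patients, not lesions, are randomised, so barring crossover all lesions of a patient fall in the same arm. Positive within-patient correlation then makes the true standard error of a treatment comparison larger than an ordinary t-test or χ2-test reports. Confidence intervals come out too narrow and p-values too small. At stake are the secondary angiographic comparisons, lesion and device success, and any per-lesion version of late loss. The primary test is not at stake.

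**Working it through.** **Step 1. The primary analysis, for reference.** Inputs from Sample size calculation: "we assumed a mean late loss of 0.3 mm (SD 0.54 mm) for both stents"; "with a 0.2 mm non-inferiority margin, type I error at 0.05 (one-sided), 90% statistical power"; allocation 2:1; 30% dropout; 375 patients in total.

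- Control arm: (1 + 1/2) × (1.645 + 1.282)² × 0.54² / 0.2² = 93.7, so 94. Test arm: 188. Total: 282 evaluable patients.
- Allowing for dropout: 282 / 0.70 = 403, or 282 × 1.30 = 367. The stated 375 is close only to the second.
- Expected evaluable: 375 × 0.70 = 262.5 (87.5 + 175). Standard error = 0.54 × √(1/87.5 + 1/175) = 0.0707. Power = Φ(0.2/0.0707 − 1.645) = 88.2%.

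This calculation counts patients and so matches one lesion per patient. The observations are independent and the t-test keeps its nominal 5% level. The gap between 88.2% and 90% comes from how dropout was added, not from how the lesion is chosen.

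**Step 2. Which endpoints have protection against clustering.**

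| Endpoint | One-lesion rule stated? | Test named | Correction named? |
|---|---|---|---|
| In-stent late loss (primary) | Yes | t-test | Not needed |
| In-stent late loss, per lesion | No | None specific to this analysis | No |
| In-segment late loss | No | None specific to this endpoint | No |
| Percentage diameter stenosis | No | t-test or χ2-test | No |
| Binary restenosis | No | t-test or χ2-test | No |
| Device and lesion success | No | χ2-test | No |

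**Step 3. Size of the effect if the named tests are run on all lesions.** The article gives neither input, so both are assumptions: a share f = 0.2 to 0.4 of patients with two lesions (the rest with one), and a within-patient correlation ρ = 0.1 to 0.5.

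Design effect: DE = 1 + (Σm²/Σm − 1) × ρ, where m is lesions per patient. With one or two lesions, Σm²/Σm = (1 + 3f)/(1 + f), so DE = 1 + [2f/(1 + f)] × ρ.

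True size of a nominal two-sided 5% test: 2 × [1 − Φ(1.96/√DE)].

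| f | ρ | DE | 1.96/√DE | True two-sided size |
|---|---|---|---|---|
| 0.2 | 0.1 | 1.033 | 1.928 | 5.4% |
| 0.2 | 0.5 | 1.167 | 1.815 | 7.0% |
| 0.4 | 0.1 | 1.057 | 1.906 | 5.7% |
| 0.4 | 0.5 | 1.286 | 1.729 | 8.4% |

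The true standard error is √1.033 = 1.02 to √1.286 = 1.13 times the reported one. If half the patients had two lesions and ρ were 0.5, DE would be 1 + (1.0/1.5) × 0.5 = 1.33 and the size about 9.0%.

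**The case against.** **The text does not tie these tests to the per-lesion analyses.** This is correct. The per-lesion sentence gives no method, and the tests are listed by endpoint. The authors clearly know about clustering, and a condensed article may leave the method for a supportive analysis, done only where feasible, to a fuller document. A reader might infer that the protocol prescribes uncorrected tests for per-lesion data, but it does not say so. What remains is more than silence. The article calls a correction necessary, exempts one endpoint from needing it, and then names only independence tests for other endpoints measured on lesions. Lesion success gives the nearest link, since it is most naturally counted per lesion, though the article does not define the unit.

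**The primary analysis.** A reader might infer that keeping one random lesion per patient is itself a flaw, because it discards data and lets the result depend on a draw. The document does not support that. The choice is deliberate, reasoned and consistent with the patient-based sample size. The draw causes no bias, and its variation is already in the t-test's standard error. A cluster-adjusted analysis of all lesions would be more precise: under the Step 3 assumptions, 262.5 × [(1 − f) + 2f/(1 + ρ)] gives the equivalent of about 280 to 348 single-lesion patients, with power of about 90–95%. However, it gives multi-lesion patients more weight and moves the target from the average patient towards the average lesion. That is a trade-off, not a correction. It should not be used to make up the dropout shortfall, and at the low end 280 is still short of 282.

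**Whether all lesions are measured.** The Quantitative coronary angiography section specifies the regions to be assessed. It does not say outright that every target lesion is measured, so it cannot be claimed that the extra data will certainly exist. The per-lesion plan makes it likely.

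**Conclusion.** The point holds for the secondary and per-lesion analyses only. The article states a need for clustering correction, meets it for in-stent late lumen loss, and leaves the other lesion-level endpoints with independence tests and no one-lesion rule. If those tests are applied to all lesions, a nominal two-sided 5% test runs at about 5.4–8.4%. This rests on the assumed 20–40% of patients with two lesions and correlation of 0.1–0.5; the article supplies neither figure. The inflation is modest at the low end and material at the high end. The primary non-inferiority conclusion is unaffected, and the one-random-lesion primary analysis should stand.

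**What to change.** In Statistical analysis, state that every comparison using more than one lesion per patient accounts for within-patient correlation. This covers percentage diameter stenosis, binary restenosis, in-segment late loss, device and lesion success, and per-lesion late loss. Use either:

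- GEE with robust variance or a mixed model with a random patient effect, and logistic GEE for binary outcomes, in place of the uncorrected t-test or χ2-test; or
- the one-random-lesion rule extended to these endpoints, in which case the simple tests remain valid.

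An all-lesion, cluster-adjusted analysis of in-stent late loss may be added as a sensitivity analysis, labelled as giving multi-lesion patients more weight.

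The cost is a little more analysis code and slightly wider intervals for the affected endpoints. No extra patients, visits or measurements beyond the per-lesion plan are needed.

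### The 92% superiority power assumes complete angiographic follow-up; with the protocol's own 30% dropout it is about 80%

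*Protocol article*

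**What the plan says.** Everything needed is in the Sample size calculation section of the protocol article. For the variability it states "we assumed a mean late loss of 0.3 mm (SD 0.54 mm) for both stents". The non-inferiority calculation is set up "with a 0.2 mm non-inferiority margin, type I error at 0.05 (one-sided), 90% statistical power". Allocation follows a "2:1 sampling ratio (Orsiro SES:ZES-I"), while for missing angiograms the section allows for "an expected 30% dropout rate (at the 9-month follow-up angiography"). The result is "a total of 375 patients (Orsiro SES, 250; ZES-I, 125) were deemed necessary to execute this study".

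A superiority test follows if non-inferiority is met, and for that test the section says: "This number of patients would also have 92% power to detect superiority with an in-stent late lumen loss difference of 0.2 mm". The alpha for this comparison of the two arms is 0.05, two-sided. No other SD and no other dropout rate is given for it.

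Two further statements fix the number of observations. The Quantitative coronary angiography section defines late loss as the change in minimal lumen diameter from after the procedure to follow-up, so it needs a follow-up angiogram. The sample size section says that "only one randomly selected lesion will be used in the analysis of in-stent late lumen loss", so each patient contributes at most one value.

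**The concern.** The section makes two power statements about the same endpoint in the same patients, and they do not fit together. For non-inferiority the signal is the 0.2 mm margin with a true difference of zero, tested at one-sided 5%. For superiority the signal is a 0.2 mm true difference, tested at two-sided 5%, which is 2.5% in each tail. The signal and the standard error are the same, but the superiority critical value is stricter (1.960 against 1.645). On one set of evaluable patients, superiority power must therefore be the lower of the two. The article has it higher, 92% against 90%, which suggests that dropout was allowed for in one calculation and not in the other.

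What is at stake is how the secondary superiority test is presented. A reader would take its planned type II error to be about 8% when the plan's own assumptions imply about 20%, and might give a non-significant superiority result more weight than it deserves.

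**Working it through.** **Inputs** (Sample size calculation section unless noted)
- SD σ = 0.54 mm in both arms; difference δ = 0.2 mm; two-sided α = 0.05, so z = 1.960
- Randomised: 250 and 125
- No angiogram at 9 months: 30%
- Test: independent-sample t-test. The Statistical analysis section names it for non-inferiority; I assume the same test for superiority.

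**Formulas**
- SE = σ·√(1/n₁ + 1/n₂)
- Normal-approximation power = Φ(δ/SE − 1.960). The noncentral-t result is given beside it.

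**Step 1. Reproduce the stated 92% (all 375 measured).**
- SE = 0.54·√(1/250 + 1/125) = 0.0592
- δ/SE = 3.381; Φ(3.381 − 1.960) = Φ(1.421) = 92.2%
- Noncentral t: 92.1%

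The stated figure is reproduced with no dropout. It does not survive even modest loss: with 10% dropout, noncentral-t power is 89.2%.

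**Step 2. Apply the stated dropout.**
- 0.70 × 250 = 175; 0.70 × 125 = 87.5, taken as 87; total 262
- SE = 0.54·√(1/175 + 1/87) = 0.0708
- δ/SE = 2.823; Φ(2.823 − 1.960) = Φ(0.863) = 80.6%
- Noncentral t: 80.3%. With 88 instead of 87 in the smaller arm it is 80.6%.

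**Step 3. Size of the gap.**
- Power: 92.1% − 80.3% = 11.8 percentage points
- Type II error: 19.7% against 7.9%, a ratio of about 2.5
- Difference detectable with 92% power at 262 evaluable: (1.960 + 1.405) × 0.0708 = 0.238 mm
- Evaluable patients needed for 92% power at 0.2 mm: smaller arm n = (1.960 + 1.405)² × 0.54² × 1.5 / 0.2² = 123.8, so 124; total 3 × 124 = 372; randomised 372/0.70 ≈ 532. If all 375 must be evaluable, 375/0.70 ≈ 536.

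**Step 4. Could another reading give 92% at 262 evaluable?**
- One-sided 5% instead of two-sided: about 88%
- Equal allocation of the same evaluable total: about 85%
- A smaller SD: it would have to be about 0.45 mm, and the article gives only 0.54 mm

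None of these readings matches the stated assumptions and gives 92%.

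**Step 5. The two power statements side by side** (normal approximation)

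| Evaluable | Non-inferiority, one-sided 5% | Superiority, two-sided 5% |
|---|---|---|
| 250 : 125 | 95.9% | 92.2% |
| 175 : 87 | 88.0% | 80.6% |
| Article states | 90% | 92% |

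The article's 92% belongs to the first row, and its 90% lies close to the second. The two statements rest on different numbers of patients, and the text does not say so.

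**The case against.** The sentence refers to the number of patients, that number is 375, and 375 late-loss values do give 92%. On this view nothing was miscalculated; a step was left out. That is fair as a description of how the figure arose, but the 375 already includes the patients expected to have no endpoint value, so it is the wrong number for a power statement.

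The intention-to-treat rule in the Statistical analysis section keeps all randomised patients in the analysis sample. This does not rescue the figure: it defines who belongs to the comparison but does not supply a measurement where there was no angiogram. The article states no imputation.

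The stronger objection concerns importance. Superiority is tested only after non-inferiority, and the 92% came after the sample size was fixed and determines neither it nor the margin, the alpha or any analysis. About 80% is a usual power level. Planned power does not enter the final confidence interval, from which precision will be judged. The article also nowhere proposes to read a failed superiority test as equality, so the risk of over-reading is a possibility rather than something the plan invites. All of this stands and limits the weight of the point. It does not make the figure right.

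Finally, 20% is a planning value. It holds for a true difference of 0.2 mm, an SD of 0.54 mm and 30% dropout; the error rate in the trial depends on what is actually observed.

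**Conclusion.** The concern holds. Under the article's own assumptions, superiority power for a 0.2 mm difference is about 80% (80.3% to 80.9% across t and normal methods and rounding of the smaller arm to 87 or 88), against a stated 92%. The overstatement of 11 to 12 percentage points is well beyond rounding or choice of method. It rests on SD 0.54 mm, two-sided alpha 0.05, 2:1 allocation, one lesion per patient, no imputation of late loss, and 30% dropout spread equally over the arms.

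This is an error in a stated figure for a conditional secondary test. It does not affect the primary non-inferiority test, the sample size or the conduct of the trial.

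**What to change.** Replace the power sentence with wording such as: *Allowing for 30% of patients without follow-up angiography (about 262 evaluable), the trial has about 80% power to detect superiority for a 0.2 mm difference in in-stent late lumen loss at a two-sided alpha of 0.05.* If the 92% is kept, label it as assuming complete angiographic follow-up and give the 80% beside it.

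Once 262 is in print, the 90% non-inferiority figure should be reconciled with it. With 262 evaluable that power is about 88%. For 90%, the smaller arm needs (1.645 + 1.282)² × 0.54² × 1.5 / 0.2² ≈ 93.7, so 94; that is 3 × 94 = 282 evaluable, or 282/0.70 ≈ 403 randomised. This is a separate and smaller discrepancy that already exists in the text, but correcting one sentence will make it visible.

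The cost is one or two sentences and a less favourable figure. No change to sample size, data collection or analysis is needed.
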